## 5. PBM Therapy Intervention, Dose Parameters, Application Sites, and Safety

The device to be used is the ProSeries device (SYMBYX Pty Ltd., Sydney, Australia) multi-diode 904 nm array (Figure 1). 

Treatment dose parameters with the PBM device will be applied as shown in Table 1.

A trained operator will administer the PBM. Dosing and application protocols for the study are based on previous studies by one of the authors ([name]). At each weekly appointment, PBMt application will be on the abdomen (9 sites) and bilateral anterior thigh (6 sites on left and right leg) (Figure 2).

The flow diagram in Figure 3 illustrates the flow of the participants through the study. 

### PBM Safety

Photobiomodulation therapy (PBMt) is a safe, non-invasive, non-pharmacological method for treating a range of symptoms and signs across a range of conditions. Sensitivity to light has been reported in 2–15% of PBM trials participants, in the form of temporary dizziness, increase in pain, tiredness, or euphoria. Several studies have concluded that there are no long-term adverse effects of PBM in vitro [28], in vivo, including non-human primates [29], and in human models [30,31,32]. We therefore do not expect the participants to experience any adverse events. However, should this occur, the participants will be provided with advice and care by their doctor as required; the event will be recorded as part of the study outcomes; and the institutional human research ethics committee will be informed.

## 6. Study Outcomes and Procedures

Outcomes chosen for the study are valid, reliable, and routinely used in the setting of IBD and chronic illness. 

### 6.1. Study Outcomes

During the first and each subsequent assessment, participants will be seated comfortably, and will complete the following questionnaires:The primary outcome measure will be the Functional Assessment of Chronic Illness Therapy—Fatigue (FACIT-Fatigue) scale, designed to assess fatigue and its impact on daily activities and functioning in chronic diseases over the past week. Thirteen items (taking two minutes to complete) include tiredness, weakness, listlessness, lack of energy, and the impact of these feelings on daily functioning, such as sleeping and social activities [33]. The psychometric properties of the FACIT-Fatigue scale have been established in a range of chronic health conditions, including Parkinson’s disease, kidney dialysis, cancer, stroke, HIV, and iron-deficiency anaemia. In the latter, the scale was found to be stable over time (ICC = 0.87), internally consistent (α = 0.93), and it demonstrated convergence with other conceptually relevant scales such as SF-36 Vitality sub-score (r = 0.74) [33].The DASS is a validated questionnaire that consists of three scales measuring depression, anxiety, and stress [34]. The short version, DASS 21 questionnaire, will be used in the study as its validity is comparable with the long version and it will be easier for the participants to complete.Short Form-36 measures health-related quality of life (36 items taking 7 min to complete). Published reliability statistics for the SF-36 have exceeded the minimum standard of 0.70 recommended for measures used in group comparisons and have exceeded 0.80 in many studies. Reliability estimates for the physical and mental summary scores usually exceed 0.90. Reliability coefficients for the SF-36 scales and summary measures have been replicated across more than 20 patient groups [35].International Physical Activity Questionnaire (IPAQ) is a 7-day recall tool that measures domains of physical activities people do as part of their everyday lives (i.e., activities at work, as part of house and yard work, transport from place to place, and in spare time for recreation, exercise or sport) (27 items taking 8 min if all items require answering). The IPAQ has been validated in many studies [36], which demonstrated that Intraclass correlation coefficients (ICC) were stable between days and the ICC for total activity scores was highest at 0.93 (CI: 0.86 to 0.97). Total activity scores were also significantly related to pedometer step counts (Pearson r = 0.66, *p* < 0.01).Patient-specific Functional Scale (PSFS) quantifies activity limitation and assesses function, allowing patients to nominate any activity they may have difficulty performing due to their health condition. The PSFS takes 3 min to complete. The PSFS has been used extensively and found to be psychometrically and clinimetrically sound in a range of clinical populations with musculoskeletal conditions [37].

Participants will be provided with a ‘sampling kit’ during the first appointment and prior to each subsequent assessment. The sampling kit will contain the pathology request slips for blood (erythrocyte sedimentation rate (ESR) and C-reactive protein (CRP)) and stool samples (faecal calprotectin (FCP)) as part of standard care; and the stool sampling requirements for microbiome analysis by a commercial entity (Microba Life Sciences, Brisbane, Australia). 

Participants will be advised on how to collect stool samples at home prior to the assessment appointment. After study assessments (and/or treatment) have been completed, the participants will be advised to attend pathology for drawing of blood samples, and to deliver the FCP stool sample. Once pathology results become available in the patient record, these will be copied by the research assistant across to the study Excel data sheet in coded form. 

Stool samples for microbiome analysis will be collected by participants at home using the Microba sampling kit, received by the investigator at the relevant appointment, coded and placed securely by the researcher in a −80 °C freezer sample storage in a PC2-compliant laboratory. Samples will be analysed as a ‘job lot’, including DNA extraction, library preparation, shotgun metagenomic sequencing to target depth of 3 Gb, and taxonomic and functional profiling. 

During the first, baseline appointment (taking approximately one hour), consenting participants will be provided with a self-report pain diary (numeric pain rating scale) which they will complete on a weekly basis. After the first appointment, the participant enters a control period of 10 weeks during which no further study-related appointments will be scheduled.

After 10 weeks of no PBM intervention, the pain diary will be gathered from participants and replaced with a new diary to complete in the following 10 weeks during the treatment phase. The same questionnaires and sample collection completed at the first appointment will be repeated at the second assessment appointment. PBM treatment will commence at the second assessment appointment which will take approximately one hour.

The intervention phase consists of 10 PBM treatments, once weekly. Consenting participants will attend at a regular clinic time to receive PBM intervention. Each appointment will take 30 min. At each appointment, participants will be reminded to complete the self-report pain diary, and this will be checked for compliance.

At the end of the treatment phase all questionnaires will be repeated, physical measures will be re-assessed, and self-report pain diaries retrieved from participants. Participants will be asked to complete the post-PBM evaluation survey to establish the acceptability/tolerability of the study requirements and intervention. The survey will contain a mixture of questions including open-ended free text questions regarding PBM acceptability and their views of any changes they experienced as a result of the intervention.

After the post-PBM appointment, participants will enter a second observational (no PBM treatment) period of 10 weeks during which they will continue to complete a weekly study pain diary.

The study will end after 30 weeks, when all questionnaires will be repeated, measures will be re-assessed (final blood and stool samples collected) and self-report diaries retrieved from participants before they exit the study.

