### Hypotheses

**Hypothesis** **1.***PBM intervention will be feasible and acceptable*.

**Hypothesis** **2.***PBM intervention will result in significantly improved fatigue scores post-intervention*.

**Hypothesis** **3.***PBM will decrease depression and increase QoL*.

**Hypothesis** **4.***PBM will result in decreased abdominal and joint pain, increased physical activity, and physical function*.

**Hypothesis** **5.***PBM intervention will be associated with decreased inflammatory burden*.

**Hypothesis** **6.***PBM intervention will be associated with an increase in the alpha diversity of the gut microbiome with an increase in the number of known beneficial bacteria and decrease in number of potentially pathogenic genera*.

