## 4. Materials and Methods

This is a prospective, single-arm pilot study. The study is designed as a pre–post study with three phases, each with a duration of ten weeks, and four data collection points. The three study phases include a 10-week observation period, followed by a 10-week PBM intervention phase during which the participants will receive weekly PBM, and the study concludes with a second 10-week observation or washout phase. Data collection points include baseline, pre-PBM, post-PBM, and the final collection point, 10 weeks after the completion of the PBM intervention. The purpose of the post-intervention observational period is to record and evaluate any sustained effects of PBM. The study duration is expected to be up to 12 months, from commencement of recruitment to end of data collection of the final participant. Rolling recruitment will be used until the required sample of 28 is achieved. 

The primary outcome of interest will be fatigue while secondary outcomes will include depression, pain, quality of life, inflammatory markers, and microbiome characterisation (of phyla and genera), physical activity, and physical functioning. All outcome measures, other than pain, will be assessed at the 4 data collection points. Pain will be assessed weekly as evidence shows that this frequency will provide most accurate assessment. 

Feasibility of the study procedures and PBM intervention will be assessed by the participants’ attendance, their views of PBM, recruitment, and attrition rates. Mixed-effects linear regression modelling will be used to assess the effect of PBM on continuous, outcome measures. We will use the intention-to-treat principle in that we will include everyone in the analysis, whether they complete the treatment or not. We will also conduct sensitivity analysis that only includes those who completed the per-protocol intervention and will report the proportion of participants lost to follow-up.

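### The sampling text allows the week-10 pre-PBM ESR and CRP blood to be drawn after the first PBM session

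*Protocol article*

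**What the plan says.** Section 4 names four time points: "Data collection points include baseline, pre-PBM, post-PBM, and the final collection point, 10 weeks after the completion of the PBM intervention". The abstract places the pre-PBM point after the 10-week control period and the post-PBM point at 20 weeks.

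Section 6.1 describes the sampling. A kit handed out at the first appointment, and ahead of each later assessment, holds the request slips for ESR and CRP (blood) and FCP (stool). For stool: "Participants will be advised on how to collect stool samples at home prior to the assessment appointment". For blood: "After study assessments (and/or treatment) have been completed, the participants will be advised to attend pathology for drawing of blood samples".

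On the second (week-10) visit the section says: "The same questionnaires and sample collection completed at the first appointment will be repeated at the second assessment appointment". It then adds: "PBM treatment will commence at the second assessment appointment which will take approximately one hour". On the course of treatment: "The intervention phase consists of 10 PBM treatments, once weekly".

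The blood markers serve Hypothesis 5, that "PBM intervention will be associated with decreased inflammatory burden". Section 3 lists ESR, CRP and FCP as the measures of inflammation. The abstract says inflammation levels will be analysed by mixed-effects linear regression to assess the PBM effect.

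**The concern.** Week 10 does two jobs in this single-arm design. It closes the control period and it is the reference from which change under PBM is measured. Section 7 relies on the untreated first period to limit the placebo problem. A week-10 value taken after a PBM session is not a clean end to the control period or a clean start to the treatment period. Any early response to that session would enter the two period changes with opposite signs.

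Two further inconsistencies follow. Markers that share one nominal time point could lie on different sides of first exposure, with stool before it and blood after it. And if some participants have blood taken before treatment and others after, the pre-PBM label would cover a mixture that cannot be separated later unless draw times are known.

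**Working it through.** No figure in the article bears directly on this point, so the check is mainly a reading of the passages side by side. The one planning figure, 24 evaluable participants for a two-sided paired t-test (effect size 0.60, alpha 0.05, 80% power; Section 6.5), reproduces: exact power at n = 24 is 0.804. It is not in question here.

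**Step 1. Which assessment visits include treatment?**

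| Visit | PBM described at this visit? | Source |
|---|---|---|
| Week 0, baseline | No; the control period follows | Section 6.1 |
| Week 10, pre-PBM | Yes; the first session | Section 6.1 |
| Week 20, post-PBM | None described | Abstract, Section 6.1 |
| Week 30, final | No; end of second observation period | Section 6.1 |

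Ten weekly sessions starting at week 10 put the tenth at week 10 + 9 = 19, and the abstract places the post-PBM assessment at week 20. Week 10 is therefore the only assessment visit the text describes as including treatment, and the words in brackets in the blood-draw sentence apply most naturally there.

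**Step 2. Which samples could be exposed at week 10?**

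| Measure | When taken | Relation to first session |
|---|---|---|
| ESR, CRP | At pathology, after assessments and/or treatment | After it, or possibly before it |
| FCP stool | At home before the visit; only delivery is later | Before |
| Microbiome stool | At home; handed over at the visit | Before |
| Questionnaires, including FACIT-Fatigue | At the visit; not covered by the blood-draw sentence | Not shown to be affected |

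So two of the three inflammation markers are concerned, after at most 1 of 10 sessions. The number affected lies between 0 and all 28.

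**Step 3. What would it do to the estimate?** Let D be the true change in a marker from an unexposed week-10 value to week 20. Let f be the share of D already present when the week-10 blood is drawn. The recorded change is then

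week 20 − week 10 = D − f·D = (1 − f)·D.

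The article gives no value for f and no expected effect on ESR or CRP. Purely by assumption, f = 0 leaves D unchanged, f = 0.1 gives 0.9·D and f = 0.3 gives 0.7·D. A short-lived reaction in the opposite direction (f below 0) would inflate the change instead. Neither the sign nor the size of f can be taken from the article.

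**The case against.** The strongest reply is that the blood-draw sentence is generic. It covers all assessment visits, including those without PBM, and its and/or leaves room for a draw after the questionnaires but before treatment. The pre-PBM label, and the order in which Section 6.1 mentions sample collection and then the start of PBM, suggest that an unexposed sample was intended. An article may also leave visit-level detail to the full protocol, and the flow diagram is not shown.

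Much of this stands. The text permits a post-treatment draw rather than compelling one, and the lack of a stated window or time recording is not by itself a fault in an article. What does not fall away is that the article states a sampling order, and that order is unsuitable at the one visit where assessment and first treatment coincide. Intent shown by a label does not tell a research assistant when to send the participant to pathology.

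A reader might infer three stronger things that the article does not support:

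- **That all 28 week-10 samples are exposed.** The wording allows anything from none to all.
- **That the effect is attenuated by a known amount, doubled in a contrast that subtracts the control-period change.** This needs an assumed f and a contrast the protocol does not specify; it states only mixed-effects linear regression.
- **That Hypothesis 5 has no clean reference.** Week-0 ESR and CRP are unexposed, and so is the pre-PBM FCP.

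**Conclusion.** The point holds as a defect of wording with a possible, unquantified effect on two secondary markers. Section 6.1 directs, or at least permits, week-10 ESR and CRP to be drawn after the first PBM session and recorded as pre-PBM, with timing that may vary between participants. The conclusion rests on reading the blood-draw sentence together with the start of PBM at the same visit, and on no other text fixing the order.

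The bias may be near zero, because one session of ten may do little to these markers. If PBM lowered them early, the recorded pre-post change would be too small rather than too large. FCP, microbiome, week-0 blood, the primary fatigue outcome and the sample size are not shown to be affected. This is a minor correction and not a condition for proceeding. It is still worth making, because an unexposed sample cannot be recovered after the visit.

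**What to change.** Amend the blood-draw sentence in Section 6.1 so that the week-10 visit is treated separately, for example: *At the pre-PBM assessment, blood for ESR and CRP is drawn before the first PBM session; at the other assessments it is drawn after the assessments are complete.* Record the date and time of each draw so that its position relative to PBM can be verified. For any participant already past week 10, establish from the pathology record, where possible, whether the draw came before or after the first session, and report how many fall on each side.

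The cost is small. The kits with request slips already go out before each later assessment, so no new material or visit is needed. Participants may have to attend pathology earlier on the day or on a preceding day, which is a slight scheduling burden. Sample size, visit schedule and treatment are unchanged.

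### Pain-diary reminders and compliance checks are tied to the PBM appointments, so diary completeness and timeliness may differ between the treatment phase and the comparison phases

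*Protocol article*

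**What the plan says.** Section 4 of the protocol article describes a single-arm study: "The study is designed as a pre–post study with three phases, each with a duration of ten weeks, and four data collection points". Pain is the one outcome not confined to those four points: "Pain will be assessed weekly as evidence shows that this frequency will provide most accurate assessment".

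Section 6.1 sets out how the diary is handled:

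- **Baseline.** "consenting participants will be provided with a self-report pain diary (numeric pain rating scale) which they will complete on a weekly basis".
- **Weeks 0-10.** "the participant enters a control period of 10 weeks during which no further study-related appointments will be scheduled". The diary is then collected: "After 10 weeks of no PBM intervention, the pain diary will be gathered from participants and replaced with a new diary".
- **Weeks 10-20.** "The intervention phase consists of 10 PBM treatments, once weekly", and for these visits: "At each appointment, participants will be reminded to complete the self-report pain diary, and this will be checked for compliance".
- **Weeks 20-30.** Participants receive no PBM and "they will continue to complete a weekly study pain diary". The diary is handed in at the end of the study.

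Hypothesis 4 is that PBM reduces abdominal and joint pain. The Discussion offers the untreated first 10 weeks as the means of limiting the placebo problem.

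**The concern.** There is no parallel control group. Any evaluation of Hypothesis 4 has to set pain during or after PBM against pain in an untreated period of the same participants, and that works only if pain is recorded under like conditions on both sides. The instrument and the nominal frequency stay the same. What changes at week 10 is whether anyone reminds the participant and checks that the diary is being filled in. In the untreated first phase an entry can be skipped, or written from memory, for up to 10 weeks before anyone looks. In the PBM phase a gap would normally be noticed within about a week.

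Measurement condition and treatment phase therefore coincide, and no later analysis can fully separate them. If participants are more (or less) likely to make an entry in a bad week, or remember bad weeks differently, part of any phase difference in pain comes from how it was recorded. The results are meant to inform whether to run a randomised trial and how large to make it, so a distorted pain contrast could carry forward.

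**Working it through.** **Procedures side by side (Section 6.1)**

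| | Weeks 0-10 | Weeks 10-20 (PBM) | Weeks 20-30 |
|---|---|---|---|
| Instrument | Weekly numeric-scale diary | Same | Weekly diary continues |
| Study visits within the phase | None, stated explicitly | Weekly | None described |
| Reminder | None described | At each appointment | None described |
| Compliance check | None described | At each appointment | None described |
| Diary collected | Once, week 10 | End of treatment phase | Once, week 30 |

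For weeks 0-10 the absence of appointments is stated. For weeks 20-30 the absence of contact is inferred from silence.

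**Share of entries**

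With 28 participants (Section 6.5) and 30 weekly entries each, 28 × 30 = 840 entries are planned. The PBM phase holds 28 × 10 = 280. The other phases hold 28 × 20 = 560, and 560/840 = 67%. This counts exposure to the unprompted condition and says nothing about bias.

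**Size of a possible bias (illustration; all inputs assumed unless noted)**

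The protocol gives no figure for pain, so there is none to reproduce. I take 24 evaluable participants from Section 6.5. That number reproduces: a two-sided paired t-test with effect size 0.60 and alpha 0.05 has exact power 0.804 at n = 24 and 0.785 at n = 23.

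- Weekly pain = the participant's own mean (average 4, between-person SD 2) plus independent weekly variation (SD 1.5). Scores are treated as unbounded.
- No true PBM effect, 10 weekly scores in each of two phases, and all PBM-phase entries completed.
- In the control phase, the log-odds of completing an entry = logit(p) + b × (that week's pain minus the participant's own mean). Here p is completion in an average week. b = 0.25 and b = 0.5 are odds ratios of exp(0.25) = 1.28 and exp(0.5) = 1.65 per point.
- Analysis: each participant's PBM-phase mean minus the mean of completed control-phase entries, t-test at 5%, 3,000 simulated trials.

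| Control-phase completion p | b = 0 | b = 0.25 | b = 0.5 |
|---|---|---|---|
| 90% | 0.01 (type I error 0.045) | -0.06 (0.07) | -0.13 (0.15) |
| 70% | 0.00 (0.053) | -0.17 (0.18) | -0.32 (0.52) |
| 50% | 0.00 (0.048) | -0.28 (0.34) | -0.50 (0.80) |

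Check by approximation: for small b, completed control-phase entries overstate mean pain by about b × (1 - p) × 1.5². At p = 0.7 and b = 0.25 this is 0.25 × 0.3 × 2.25 = 0.17, which agrees with the table.

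Three things follow:

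1. With b = 0 there is no bias, however many entries are missing.
2. With b above zero the error favours PBM. If high-pain weeks are the ones skipped, b is negative and the sign reverses.
3. A mixed model on the recorded entries does not remove the error, because completion depends on the score that was not recorded.

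**The case against.** The strongest reply is that the document is a journal article condensing a fuller protocol. Having no appointments does not exclude text or e-mail reminders, and such logistics are often left out of an article. This stands in part. The gap in weeks 20-30 is silence, and the full protocol may fill it. But the article does describe diary reminders and checks, places them at the PBM appointments, and states that the first phase has no appointments. The contrast between those two phases is a described procedure.

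It is also fair that Hypothesis 4 names no contrast, that the abstract's list of mixed-model outcomes omits pain, and that the authors already concede that placebo cannot be excluded and that a randomised trial would be needed. These points lower the stakes. They do not make recording alike across phases, which placebo caveats do not cover.

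A reader might infer more than the text supports:

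- **That the treating team reads the scores and so puts social pressure on them.** The article mentions a compliance check only. It does not say who does it or that scores are discussed, and staff collect the diaries from every phase.
- **That the diary is on paper, or that PBM-phase entries are made on time.** Neither is stated. A weekly check limits back-filling but does not exclude it. At the first session the diary is newly issued and has nothing to check.
- **That counts of affected entries show the damage.** Assuming 30% missing or late without prompts and 5% with them gives 0.30 × 560 = 168 against 0.05 × 280 = 14. The rates are invented, and the denominators turn a 6-fold ratio of rates into a 12-fold ratio of counts. Neither figure measures error in pain scores.

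**Conclusion.** The point holds in a limited form. As written, diary reminders and checks coincide with the PBM phase, so completeness and timeliness may differ between that phase and the untreated phases. The asymmetry is firm for weeks 0-10 and inferred for weeks 20-30.

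It becomes bias only if completion or recall is related to pain. The direction is unknown, and the document gives nothing from which to fix the size. On the assumed inputs above, the spurious difference runs from nil to about half a point on the numeric scale, and it stays small at 90% completion. It would go too far to say that a change in pain cannot be attributed to PBM because of the diary procedure: the procedure adds a possible source of error, and attribution is already limited by the single-arm design.

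Pain is a secondary outcome. FACIT-Fatigue is collected at the four assessment appointments and is untouched, and no sample-size figure changes. This should be corrected because correction is cheap and the data could not settle the question afterwards, but it does not undermine the study's main purpose.

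**What to change.** - Use one diary procedure for weeks 0-30: the same automated weekly remote prompt, a dated entry, and the same completion check in all three phases. Let this replace the reminder and check at the PBM visits, so that contact about the diary does not change with treatment.
- Report the proportion of entries completed and how late they were, by phase, beside the pain results.
- Keep all entries in the main pain analysis. Excluding those made later than a preset number of days should be a sensitivity analysis only, because as a main rule it could itself create missing data that differ by phase.
- If the full protocol already provides equivalent prompts in both untreated phases, a sentence saying so resolves the point.

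The cost is the small effort of setting up the message and monitoring replies and dates. No visits are added.

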### 4.2. Participant Selection

Since this is a study of PBM in young adults with IBD, main eligibility criteria will include participants’ age, confirmed IBD diagnosis and the presence of fatigue. 

Inclusion Criteria: Age 18–35 years.Diagnosis of IBD made by gastroenterologist.Fatigue symptoms (FACIT F score < 30).Verbal and written English proficiency that will enable them to participate.Ability to provide informed consent.Patients of the IBD outpatient clinics at Mater Hospital.Individuals who are able to attend the 10 weekly PBM treatment sessions as well as the additional sessions at the baseline and at the end of the study.

Exclusion Criteria:

Individuals with major psychiatric illness (psychosis, Post-Traumatic Stress Disorder, substance abuse/dependence) as its treatment and symptoms could prevent participation in the programme.Individuals without conversational or written English.Major surgery booked in the next 6 months as this would preclude participation.Pregnant women, as there are no studies to date of PBM in pregnancy.

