### 6.5. Sample Size Calculation

We have calculated that the sample size required to achieve 80.0% power to reject the null hypothesis, for the effect size of 0.60 and a significance level (alpha) of 0.050, using a two-sided paired t-test, will be 24. From researchers’ experience, the most likely dropout rate in this type of study is between 5–10%. Considering the 5–10% dropout, we will therefore aim to recruit a total sample size of 28.

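### The safety section cites transient reactions in 2–15% of participants yet expects no adverse events, and the only acceptability survey comes at the end of treatment, so participants lost earlier are not heard.

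*Protocol article*

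**What the plan says.** **Safety.** The PBM Safety part of section 5 states: "Sensitivity to light has been reported in 2–15% of PBM trials participants". The forms it lists are short-lived dizziness, more pain, tiredness and euphoria. The next sentence cites studies that found no long-term adverse effects. The conclusion drawn is: "We therefore do not expect the participants to experience any adverse events". Should an event occur anyway, it is to be recorded among the study outcomes and reported to the ethics committee. Section 6.3 says that all adverse and serious adverse events go into the trial database.

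**Acceptability.** Section 3 makes acceptability and feasibility the primary objective. It has a quantitative part (attendance, attrition and drop-out) and a qualitative part (participants' views, from the post-PBM questionnaire). Section 4 adds recruitment. Section 6.1 places the questionnaire at the end of the treatment phase: "Participants will be asked to complete the post-PBM evaluation survey to establish the acceptability/tolerability of the study requirements and intervention". The article describes no other occasion for it.

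**Size.** Section 6.5: "we will therefore aim to recruit a total sample size of 28", allowing for dropout, where "the most likely dropout rate in this type of study is between 5–10" per cent.

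**The concern.** The safety section moves from one kind of evidence to a different kind of conclusion. Absence of lasting harm says nothing about transient reactions, which the same paragraph has just put at up to 15%. A reader who takes the conclusion at face value expects a clean record and has little reason to ask about reactions.

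This matters here because two of the four listed reactions, tiredness and more pain, overlap with study outcomes: fatigue is the primary outcome and pain is scored weekly. A reaction reported in passing could be put down to IBD.

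The survey raises a related problem. People who leave during treatment may have the most to say about whether PBM and the study demands were tolerable. If their views are sought only at a visit they never reach, attrition shows how many left but the survey does not show why. Both gaps bear on tolerability, which the later randomised trial would have to plan around.

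**Working it through.** **1. The plan's own sample size.** Inputs from section 6.5: effect size 0.60, two-sided alpha 0.05, power 80%, paired t-test, with the result "using a two-sided paired t-test, will be 24". Exact power from the noncentral t distribution, with noncentrality 0.60 × √n and n − 1 degrees of freedom:

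- n = 23: 78.5%
- n = 24: 80.4%

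So 24 is reproduced. Allowing for dropout, 24 / 0.95 = 25.3, rounded up to 26, and 24 / 0.90 = 26.7, rounded up to 27. The stated 28 is slightly more generous. Neither figure depends on the points below.

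**2. Reactions implied by the cited rates.** Assumptions: the 2–15% is a per-participant rate, it carries over to this device and population, and participants react independently. Expected number = N × p. Chance of at least one = 1 − (1 − p)^N.

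| N treated | p | Expected | Chance of none | Chance of at least one |
|---|---|---|---|---|
| 28 | 0.02 | 28 × 0.02 = 0.56 | 0.98^28 = 56.8% | 43.2% |
| 28 | 0.15 | 28 × 0.15 = 4.2 | 0.85^28 = 1.1% | 98.9% |
| 24 | 0.02 | 24 × 0.02 = 0.48 | 0.98^24 = 61.6% | 38.4% |
| 24 | 0.15 | 24 × 0.15 = 3.6 | 0.85^24 = 2.0% | 98.0% |

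At the low end, zero reactions is the likeliest single result. At the high end, a trial with none would be very surprising. An unqualified expectation of none is not compatible with the whole cited range.

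**3. Who the survey can miss.** The plan's dropout range gives 28 × 0.05 = 1.4 to 28 × 0.10 = 2.8 participants over the study. Only those lost before the end of treatment miss the survey. Among these, only those lost after starting PBM could have reported on the treatment itself. The number is therefore at most about 1 to 3 on the plan's figures, and the article gives no split by phase.

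**4. What the survey can cover.** It is meant to address the study requirements as well as the intervention. It is given before the third 10-week phase, which still includes weekly pain diaries, blood and stool samples and a last visit. Views on those demands cannot be in it.

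**The case against.** The strongest reply is that the trial does not depend on either weak spot.

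- *Adverse events are recorded whatever is expected.* This stands. Section 6.3 is unconditional, and participants are seen weekly. A reader might infer that reactions would go unrecorded, but the documents do not support that. They do not say how events are elicited, and the only routine check described at treatment visits concerns the pain diary.
- *Acceptability is not measured by the survey alone.* This also stands. Attendance, attrition, drop-out and recruitment are measured, so someone who leaves counts in those figures. A reader might infer that the whole answer to the primary objective is biased towards a favourable result. That is not shown.
- *Stopping PBM is not leaving the study.* Correct. Section 4 includes everyone in the analysis whether or not they complete treatment, so a participant who stops PBM but stays in follow-up can still be surveyed. Only those lost before the visit clearly miss it. An exit procedure may also exist in the full protocol, which is not shown.
- *The attendance criterion is ordinary.* Section 4.2 admits "Individuals who are able to attend the 10 weekly PBM treatment sessions as well as the additional sessions". A reader might infer that attendance is thereby made uninformative. But being able to attend is not the same as attending, and missed sessions and attrition remain observable. No finding is made on this.
- *There is no acceptability percentage to be biased.* The survey mixes question types, including free text, and the article defines no such endpoint. A numerical comparison of completers with all participants would rest on invented responses.

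What remains is the contradiction in the safety section, which needs no unseen text, and the fixed timing of the survey.

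**Conclusion.** The point holds in two limited parts.

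First, the PBM Safety section contradicts itself. Its own rates imply about 0.6 to 4 of 28 participants with a transient reaction, and a 43% to 99% chance of at least one. The evidence it cites supports, at most, an expectation of no long-term effects. These figures rest on reading 2–15% as a per-participant rate that carries over from other PBM trials, on all 28 being treated, and on the listed reactions counting as adverse events.

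Second, the qualitative part of the primary objective is collected once, at the end of treatment. The views of participants lost before then are not captured, although their loss is counted. On the plan's dropout figures this affects at most about 1 to 3 people. That is few, but they may be the most informative about tolerability. The weight of this part is reduced because the full protocol may contain an exit procedure.

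No efficacy endpoint, efficacy analysis or sample size is affected.

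**What to change.** 1. **Reconcile the safety sentences.** Limit the statement that adverse events are not expected to long-term effects. Say that transient reactions are expected at the cited rates, about 0.6 to 4 of 28 participants. Ask about the listed reactions at each of the 10 existing treatment sessions and report them as a tolerability outcome.
2. **Hear from those who leave.** Offer the same survey, or a short exit form, when a participant stops PBM or withdraws. Report survey results with all who started PBM as the denominator, and state the number of non-responders. The report should also make clear that the survey does not cover the final 10-week phase.

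The cost is one short form and one question per existing visit. The feasibility and tolerability figures may look slightly less favourable. If an exit procedure already exists in the full protocol, a sentence saying so would meet most of the second item.
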